# Short-Term Effects of Nonnutritive Sweetener (Sucralose and Saccharin) Consumption on Glycemic Control and Gut Microbiota in Patients With Type 2 Diabetes: Protocol for a Double-Blind, Randomized, Placebo-Controlled, Crossover Trial

**DOI:** 10.2196/82695

**Published:** 2025-12-10

**Keywords:** saccharin, sucralose, nonnutritive sweetener, artificial sweetener, glycemic control, gut microbiota, type 2 diabetes mellitus

## Abstract

**Background:**

Nonnutritive sweeteners (NNSs) are widely used as sugar substitutes to help individuals with diabetes manage glycemic control. However, emerging evidence suggests that even low doses of NNSs, such as saccharin and sucralose, may adversely affect metabolic health by impairing glycemic regulation, potentially through alterations in the gut microbiota. In Malaysia, where gut microbiome research is still limited, particularly among individuals with type 2 diabetes mellitus (T2DM), further investigation is warranted to inform safe and evidence-based use of NNSs.

**Objective:**

This study aims to evaluate the short-term effects of saccharin and sucralose consumption on glycemic control and gut microbiota composition in adults with T2DM.

**Methods:**

This is a double-blind, randomized, placebo-controlled, crossover trial. A total of 33 adults with T2DM will consume sucralose (5 mg/kg body weight), saccharin (2 mg/kg body weight), or a placebo (calcium carbonate) in capsule form daily for 7 days per intervention arm, with a 4-week washout period. Data collection will include anthropometric measurements, biochemical assessments for glycemic control, dietary records, physical activity levels, and stool samples. The homeostatic model assessment for insulin resistance will be used to assess insulin sensitivity, while 16S rRNA V3-V4 region sequencing will be conducted to profile gut microbiota composition.

**Results:**

Recruitment is planned to begin in January 2026 and is expected to conclude by September 2026, with study completion anticipated by March 2027. As of December 2025, no participants have been enrolled.

**Conclusions:**

This trial will contribute novel insights into the effects of short-term NNS consumption on glycemic control and gut microbiota composition in individuals with T2DM. These findings may support evidence-based recommendations for NNS use in diabetes management and enhance understanding of microbiome-diet interactions in an ethnically diverse Asian population.

**Trial Registration:**

ClinicalTrials.gov NCT07124585; https://clinicaltrials.gov/study/NCT07124585

**International Registered Report Identifier (IRRID):**

PRR1-10.2196/82695

## Introduction

Nonnutritive sweeteners (NNSs) are widely used as sugar substitutes to reduce caloric intake and help manage blood glucose levels. Although previously considered metabolically inert, emerging evidence suggests that NNSs may influence host metabolism through their effects on the gut microbiota [1]. A landmark study in 2014 demonstrated that NNS-induced glucose intolerance in mice was mediated by gut microbiota alterations and was transferable to germfree mice via fecal microbiota transplantation [2]. However, subsequent studies have reported inconsistent findings, some indicating that NNSs alter microbial composition and impair glycemic control [3-6], while others have found no significant effects [7-9]. Variability in outcomes likely reflects differences in the type of sweetener, study design, host characteristics, and baseline microbiota composition.

Although all types of NNSs are categorized as sugar substitutes, they differ in their chemical structures, metabolism, and gut accessibility. Therefore, findings from one NNS cannot be generalized to all types of sweeteners. A recent study by Suez et al [3] in 2022 showed that while all tested NNSs altered the gut microbiome, only sucralose and saccharin significantly impaired glycemic responses [3]. These effects were reproduced in germfree mice colonized with microbiota from exposed individuals, strengthening the causal link between NNSs, gut microbiota, and metabolic outcomes. Therefore, this study focuses specifically on sucralose and saccharin.

Observational studies have also raised concerns that long-term consumption of sucralose and saccharin may lead to glycemic dysregulation, increased insulin resistance, or metabolic disturbances [2,3,10-13]. However, these effects have generally been observed at higher doses and with prolonged exposure. In contrast, this study will adopt a short-term, controlled intervention using doses well within the acceptable daily intake recommended by major health authorities, including the US Food and Drug Administration (FDA), the European Food Safety Authority, and the Joint FAO/WHO Expert Committee on Food Additives [14-17]. Both NNSs have been extensively evaluated and are considered safe for human consumption within their established acceptable daily intake limits.

To date, most NNS studies have focused on healthy populations, overlooking the fact that type 2 diabetes mellitus (T2DM) itself is associated with gut dysbiosis and altered metabolic signaling [18,19]. According to the International Diabetes Federation, an estimated 4.75 million adults in Malaysia were living with diabetes in 2024 [20]. The use of NNSs in Malaysia is expected to increase due to growing public awareness of the harmful effects of excessive sugar consumption and the implementation of a sugar tax on sugar-sweetened beverages. Consequently, the food industry has increasingly turned to NNSs for product reformulation.

Given these trends and the limited evidence among individuals with T2DM, this study aims to evaluate the short-term effects of sucralose and saccharin on glycemic control and gut microbiota composition in Malaysian adults with T2DM. Specifically, the primary objective is to assess changes in insulin sensitivity, while the secondary objective is to examine alterations in gut microbiota composition and diversity following exposure to different NNSs.

## Methods

### Study Design

This study is a double-blind, randomized, placebo-controlled crossover trial. The crossover design allows each participant to serve as their own control across 3 intervention phases. Each participant will complete a 12-week protocol comprising a 1-week run-in period followed by 3 intervention phases, each separated by a 4-week washout period. A total of 6 study visits, comprising 3 preintervention and 3 postintervention assessments, will capture baseline and postintervention data. During the run-in and washout periods, participants will maintain their habitual diet and physical activity. The study will be conducted at a government primary care facility situated in an urban area. Recruitment will be facilitated through clinic listings and physician referrals. Written informed consent will be obtained after participants receive detailed verbal and written explanations of the study procedures, risks, and rights. The study timeline is summarized in Figure 1.

**Figure 1 figure1:**

Overview of the study visits.

### Participants

This study aims to recruit a cohort of clinically stable patients representative of Malaysians with early-phase T2DM. Eligible participants will be males aged 30 to 59 years, with a BMI of 23.0 to 29.9 kg/m², classified as overweight [21]. Participants must have a clinical diagnosis of T2DM for 1 to 10 years, with baseline glycated hemoglobin (HbA_1c_) below 10%, and be managed with oral antidiabetic medications only. Individuals with stable, nonsevere chronic conditions, such as hypertension or dyslipidemia, will be included if they have maintained a consistent oral treatment regimen for at least 6 months before enrollment. All participants must have previously received dietary counseling for diabetes and agree to maintain their habitual diabetes-friendly diet and regular physical activity throughout the study. They must abstain from alcohol consumption during the intervention period and be literate in either English or Bahasa Malaysia to ensure full understanding of the study procedures and informed consent materials.

Exclusion criteria focus on lifestyle or dietary patterns that deviate from typical Malaysian practices or that could substantially alter the gut microbiota. Individuals will be excluded if they currently smoke or consume alcohol, have experienced more than 5% body weight change within the past 3 months, or have acute illness or major comorbidities, such as cardiovascular, psychological, neurological, renal, or endocrine disorders other than T2DM. Those with known intolerance or allergy to the test products, adherence to special diets (eg, vegetarian, ketogenic, or intermittent fasting), or use of medications or supplements (eg, probiotics) that may affect intestinal function or microbiota composition will also be excluded. Participation in another clinical trial within the past 3 months will preclude eligibility. Participants may withdraw voluntarily or be withdrawn for safety reasons, protocol deviation, or the need for antibiotic therapy. Diabetes management will continue as per clinical practice. Adverse events will be monitored and managed by the study physician following institutional protocols.

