This trial aims to overcome these inconsistencies through a tightly controlled crossover design, enabling each participant to serve as their own control and thereby minimizing interindividual variability. A 1-week intervention period was selected to assess short-term effects while maintaining participant compliance and feasibility, followed by a 4-week washout period to avoid carryover effects. The selected NNS dosages represent the upper acceptable daily intake recommended in medical nutrition therapy guidelines, ensuring both safety and sufficient exposure to detect measurable outcomes [22]. Capsules will contain pure sucralose or saccharin to isolate the effects of the sweeteners themselves, excluding confounding components from commercial formulations. Recruitment through government health care facilities allows for a clinically characterized sample reflective of the local T2DM population. Restricting participation to males within a defined age and BMI range enhances phenotype consistency, while inclusion criteria based on disease duration and treatment regimen further standardize metabolic profiles. Gut microbiota profiling using 16S rRNA sequencing targeting the V3-V4 region will facilitate comparison with established microbiome literature [44].

Several limitations warrant consideration. The relatively short intervention period and modest sample size may not capture longer-term or subtle metabolic and microbial changes. Although participants will be encouraged to maintain their usual diet and physical activity, residual variability in lifestyle behaviors could influence outcomes. These confounders will be monitored using validated dietary and physical activity recall tools to aid interpretation. Furthermore, as limited baseline microbiome data are available for Malaysian individuals with T2DM, observed microbial shifts should be interpreted within the context of population-specific dietary and genetic factors. Nonetheless, the comprehensive baseline characterization and rigorous design of this study are expected to strengthen internal validity and provide a valuable foundation for future investigations.

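### Habitual diet is fixed in every phase with no stated limit on participants' own sweetener use, so background exposure can dilute the sweetener-placebo contrast

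*Protocol article*

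**What the plan says.** **Diet instruction.** Under Participants, the article makes it a condition of entry that participants "agree to maintain their habitual diabetes-friendly diet and regular physical activity throughout the study". Study Design repeats this for the intervals around treatment: "During the run-in and washout periods, participants will maintain their habitual diet and physical activity".

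**Exclusions.** Participants also states the purpose of the exclusions: "Exclusion criteria focus on lifestyle or dietary patterns that deviate from typical Malaysian practices or that could substantially alter the gut microbiota". The list covers smoking, alcohol, recent weight change, comorbidities, intolerance of the test products, special diets, medications or supplements that act on the gut, and recent trial participation. Sweetener use is not on it. Alcohol, by contrast, is both an exclusion and something to abstain from during the intervention period.

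**Expected background use.** The Abstract says that nonnutritive sweeteners "are widely used as sugar substitutes to help individuals with diabetes manage glycemic control". The Introduction expects use in Malaysia to increase and adds that "the food industry has increasingly turned to NNSs for product reformulation". No usage rate is given.

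**Measurement and analysis of diet.** Table 1 schedules a dietary record at screening and at all six visits. Data Collection describes 3-day food records, reviewed face to face and analysed for nutrients. Statistical Analysis allows dietary intake as a covariate where appropriate. The Discussion lists residual lifestyle variability as a limitation. None of these places names sweetener intake.

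**Dose wording.** The Introduction describes the trial as "using doses well within the acceptable daily intake recommended by major health authorities". The Discussion says: "The selected NNS dosages represent the upper acceptable daily intake recommended in medical nutrition therapy guidelines".

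**The concern.** The instruction to keep the habitual diet is normally a strength, because it holds other influences steady. Here the habitual diet may contain the exposure under test. For a regular user of sucralose or saccharin, full compliance means taking it in the placebo phase and in both washouts, and arriving at each pre-phase visit already exposed. Other sweeteners matter too for the secondary outcome: the Introduction cites a 2022 study in which every sweetener tested altered the gut microbiome.

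The entry criteria make such users plausible. All participants must have had dietary counselling for diabetes and must follow a diabetes-friendly diet.

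At stake is the reading of a null result. The closing paragraph of the Discussion expects the findings to inform dietary recommendations, policy and views on safety. If part of the sample had little contrast between phases, a finding of no difference could be taken for reassurance that the trial was not in a position to give.

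**Working it through.** **1. Inputs (Sample Size).** Cohen f = 0.25; m = 3 within-subject conditions; α = 0.05; target power 80%; correlation ρ = 0.5; minimum n = 28; recruited n = 33.

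**2. Reproduce the plan's figure.** For a one-group repeated-measures ANOVA with sphericity, the noncentrality is λ = f²·n·m/(1 − ρ), with df1 = m − 1 and df2 = (n − 1)(m − 1).

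- n = 28: λ = 0.0625 × 28 × 3 / 0.5 = 10.5, df 2 and 54, power 81.2%.
- n = 27: power 79.6%, so 28 is the minimum, as stated.
- n = 33: λ = 0.0625 × 33 × 3 / 0.5 = 12.375, df 2 and 64, power 87.8%.

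The sample size is correct on its own inputs. It assumes the full contrast between active and placebo phases in every participant.

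**3. Dilution.** Let s be the share of regular users and d the fraction of the contrast lost in a user. The average contrast scales by (1 − s·d), so f becomes 0.25 × (1 − s·d). The error variance is held unchanged. Neither s nor d is in the documents; both are assumptions. The worst case for a given share is d = 1, no contrast at all in users:

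| Share of users s | f | Power, n = 28 | Power, n = 33 | n needed for 80% |
|---|---|---|---|---|
| 0% | 0.250 | 81% | 88% | 28 |
| 10% | 0.225 | 72% | 80% | 34 |
| 20% | 0.200 | 61% | 69% | 42 |
| 30% | 0.175 | 49% | 57% | 54 |
| 40% | 0.150 | 38% | 44% | 73 |

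**4. Milder assumption.** If users lose half the contrast (d = 0.5), a 20% share gives s·d = 0.10, which is the 10% row: 72% at n = 28 and 80% at n = 33. A 40% share gives s·d = 0.20, which is the 20% row: 61% and 69%.

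**5. Direction.** Stable background use is present in all three phases of the same person. The comparison is then capsule plus background against placebo plus background. That can shrink the difference but does not favour any one arm.

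**6. Dose wording.** The Introduction measures the doses against limits set by major health authorities; the Discussion measures them against medical nutrition therapy guidelines. These are different benchmarks, and the article gives no acceptable-intake value for the health authorities, so the two statements cannot be tested against each other numerically.

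**The case against.** **The article is condensed.** A full protocol or information sheet could hold a list of foods to avoid, and heavy sweetener use might be caught under the general aim of the exclusions. This limits the claim to what the article states. It does not remove the point: the article does more than stay silent, since it instructs participants to keep the habitual diet throughout. A restriction elsewhere would have to be written as an exception to that instruction.

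**The washout is meant to clear the capsule.** Its stated purpose is to avoid carryover, and a return to each person's usual state serves that purpose. This stands. A reader might infer that the washout fails or that the crossover is invalid; the documents do not support that. Each phase has its own pre-intervention visit, and stable use is balanced within person.

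**The power loss is extreme.** Users still receive the full capsule dose on top of their own intake in the active phases, so a nil contrast would require their habitual intake to have saturated the response. Nothing in the documents supports that. This also stands, and the table is therefore a worst case for each assumed share.

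**Diet is already recorded and may be adjusted for.** True, and it makes the fix cheap. But sweetener intake is not named in the record, and recording exposure does not restore a contrast that was lost.

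**Excluding users would make the sample less typical.** Agreed. Participants sets the aim of a sample representative of Malaysians with early-phase disease, so outright exclusion is a trade-off and is not needed.

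**Conclusion.** The concern holds as a dilution problem. As written, the plan leaves regular sweetener users exposed in the placebo phase, the washouts and the pre-phase samples, although the article itself expects such use to be common. The size is unknown because no usage rate is given. Under the nil-contrast assumption, user shares of 10 to 40% reduce power for the primary comparison to between 72% and 38% at 28 participants, or between 80% and 44% if all 33 complete. Under that assumption, full completion by all 33 would absorb a user share of about 10%. Any remaining contrast in users makes the loss smaller.

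Two stronger readings should be resisted. The documents do not show bias toward any arm. Nor do they show that capsule plus dietary intake would exceed an acceptable limit: the two dose statements use different benchmarks, the health authorities' values are not given, and dietary intake is unknown. What remains there is wording to be reconciled.

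**What to change.** 1. Amend the habitual-diet instruction in Study Design and Participants so that participants otherwise keep their usual diet but avoid sweetener-containing products from run-in to Visit 6.
2. Add a sweetener item (products and servings) to the food records already scheduled at screening and every visit.
3. State in Statistical Analysis how that item defines per-protocol status.
4. Reconcile the Introduction and Discussion statements on acceptable daily intake, naming the benchmark that each one uses.

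The cost is one instruction and one record item, a small added burden for participants, and a slight departure from habitual diet. With a 1-week run-in, a regular user would have avoided sweeteners for a shorter time before the first phase than before the later ones, which the record item would let the analysts describe. The article reports no participants enrolled as of December 2025, so the change fits best before the first participant enters.

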### Intervention

Participants will receive 1 of 3 interventions: sucralose, saccharin, or a placebo, for 7 consecutive days during each intervention phase. Participants will consume the assigned capsule each morning after breakfast with plain water to standardize timing and minimize missed doses. Dosages will be adjusted based on body weight according to national guidelines, with 5 mg/kg for sucralose and 2 mg/kg for saccharin [22]. The placebo, consisting of 500 mg of calcium carbonate, will be administered under identical conditions and is considered physiologically inert at this dose [9].

Randomization and allocation concealment will be conducted by external personnel not involved in recruitment, data collection, or analysis. A computer-generated block randomization sequence will assign participants to 1 of 3 intervention orders (sucralose, saccharin, or placebo) to ensure balanced allocation across participants. All test products will be encapsulated in identical opaque capsules and packaged in indistinguishable small plastic pouches. Labeling will be performed by external personnel according to the intervention sequence, where each package will be marked as “first intervention,” “second intervention,” or “third intervention” to maintain blinding. Both participants and investigators will remain blinded throughout the data collection period. The randomization code will be securely stored and accessible only in the event of a medical emergency.

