### Sample Size

The sample size for this crossover trial was estimated based on detecting a medium effect size (Cohen *f*=0.25), consistent with findings from a recent meta-analysis of soluble fiber supplementation in T2DM, which reported moderate standardized mean differences for HOMA-IR (standardized mean difference −0.58, 95% CI −0.86 to −0.29) [23]. Using G*Power 3.1.9.6, we computed the required sample size for a within-subject repeated-measures ANOVA with 3 conditions (sucralose, saccharin, and placebo), assuming α=.05, and statistical power at 80%, and a moderate correlation (*r*= 0.5) among repeated measurements [24]. The analysis indicated that a minimum of 28 participants would be required. To account for potential dropout or noncompliance, we will recruit 33 participants.

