### Statistical Analysis

Clinical data will be presented as mean (SD) unless stated otherwise. Statistical analyses will be performed using SPSS Statistics (version 28.0; IBM Corp) [40]. The normality of continuous variables will be assessed using the Shapiro-Wilk test. Participants’ baseline characteristics will be summarized using descriptive statistics. Differences in glycemic responses across the 3 study arms will be assessed using either 1-way ANOVA or the Kruskal-Wallis test, depending on data distribution. Changes in clinical variables before and after the intervention will be analyzed using repeated-measures ANOVA, with time (before vs after), group (intervention arm), and the time-by-group interaction as factors. Sociodemographic characteristics, dietary intake, and physical activity levels will be considered as covariates where appropriate. A *P* value of <.05 will be considered statistically significant. Analyses will be conducted according to the intention-to-treat principle, with per-protocol analyses performed for participants who complete the study without major deviations. Missing data will be handled using appropriate imputation methods, and any exploratory analyses will be clearly identified and interpreted with caution.

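### Randomising to three unlisted orders out of six leaves the crossover less protected against carryover than six orders would, at the same sample size

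*Protocol article*

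**What the plan says.** The Intervention section states: "A computer-generated block randomization sequence will assign participants to 1 of 3 intervention orders". The words in brackets that follow are the three products, not three sequences, so the orders themselves are not given.

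Under Study Design, every participant takes all three products ("The crossover design allows each participant to serve as their own control across 3 intervention phases"), in a schedule of "a 1-week run-in period followed by 3 intervention phases, each separated by a 4-week washout period". Each phase has its own baseline: "A total of 6 study visits, comprising 3 preintervention and 3 postintervention assessments, will capture baseline and postintervention data". Table 1 shows blood and stool at all six visits. The Outcomes section defines both the primary outcome (HOMA-IR) and the secondary outcome (microbiota) as changes.

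The Discussion names the washout as the safeguard: "followed by a 4-week washout period to avoid carryover effects". The Statistical Analysis section describes a repeated-measures ANOVA "with time (before vs after), group (intervention arm), and the time-by-group interaction as factors". It names no term for period, sequence or carryover.

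**The concern.** Three products can be given in six orders. Using three is a stated design choice, not a detail left to another document, and it limits which product can precede which. If a sweetener leaves a residual effect beyond the washout, a design with one fixed predecessor per product loads that residual on one successor and hardly at all on the other. A comparison such as saccharin versus placebo could then partly reflect sucralose. The microbiota outcome makes this relevant, because the article's own premise is that sweeteners may act through altered gut microbiota. The article gives no data showing that four weeks is long enough for the microbiota or HOMA-IR to return to baseline.

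**Working it through.** **Inputs.** Three products, three phases, three orders, 33 recruited and 28 required (Study Design, Intervention, Sample Size). U = sucralose, S = saccharin, P = placebo. L is the carryover of a product into the next phase. The documents give no value for L, so results are per unit of L. σ² is the within-participant residual variance.

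**1. The plan's own figures.** The schedule adds up: 1 + 3×1 + 2×4 = 12 weeks. For the sample size, λ = f²·n·m/(1−r) = 0.0625 × 28 × 3 / 0.5 = 10.5, with 2 and 54 degrees of freedom. Power is 0.812, so the stated 28 is reproduced.

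**2. Which sets of three orders are possible.** There are 20 ways to choose 3 orders from 6. Exactly two put each product once in each period: {USP, SPU, PUS} and {UPS, SUP, PSU}. These two are also the only sets in which every product has a single fixed predecessor. The other 18 avoid the fixed predecessor but are unbalanced over periods.

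**3. Bias on post-phase values, no carryover term.** In {USP, SPU, PUS}, S follows U in two of the three orders and comes first in the third. The S mean therefore takes up 2/3 of a carryover from U, and the U and P means take up none. With all six orders used equally, S follows U in 2 of 6 and P follows U in 2 of 6, so each takes up 1/3. For a carryover L from sucralose:

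| Contrast | 3 cyclic orders | 6 orders |
|---|---|---|
| S − P | +2/3 L | 0 |
| U − P | 0 | −1/3 L |
| U − S | −2/3 L | −1/3 L |

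In the reverse rotation the same carryover biases U − P and S − P by −2/3 L each and U − S by 0.

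**4. Variance, by least squares with participant, period and product.**

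| Design | No carryover term | With carryover term | Ratio |
|---|---|---|---|
| 3 cyclic orders, 11 each | 2/33 = 0.0606σ² | 0.3030σ² | 5.0 |
| 6 orders, 5 each | 2/30 = 0.0667σ² | 0.0833σ² | 1.25 |

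The two rows differ in total number (33 and 30), so the ratios are what to compare. Without a carryover term both designs give 2σ²/N. The carryover model with three orders has full rank (33 + 2 + 2 + 2 = 39 columns), so carryover can be estimated, though imprecisely.

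**5. Change scores.** Let the residual be a at the next pre-phase visit and b at the next post-phase visit. The factor 2/3 then multiplies (b − a):

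- b = a: bias 0.
- b = a/2: bias −1/3 a.
- b = 0: bias −2/3 a.

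A residual that decays during the phase therefore biases the result in the opposite direction from step 3.

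**6. Six orders with 33 participants.** Five full blocks of six plus half a block give 6 in three orders and 5 in the other three. With one such split the largest bias is 0.345L, the variance without a carryover term is 0.0607σ² to 0.0608σ², and the ratio is 1.24 to 1.26. With six sequence groups, df2 = (28 − 6) × 2 = 44 and power at 28 is 0.807.

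**The case against.** A reader might infer that three orders mean each product always follows the same product, that any residual is credited to the next product, and that the washout is the only protection. The documents do not support this:

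- The orders are not listed, and a full protocol may list them. The fixed predecessor holds only for the two cyclic sets.
- Even in those sets at most 2/3 of a residual enters a contrast, and some contrasts take up none.
- Each phase has its own baseline and both outcomes are changes, so a constant residual cancels. The 2/3 figure is for post-phase values.
- Carryover can be examined without changing the orders. With 11 per order, 11 participants have had each product before Visit 3, and all have a Visit 1 value taken before any test product.

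The opposing case adds that a Latin square with a washout four times the exposure is an accepted design. It also notes that six orders only spread the bias: if both sweeteners carry over equally, {USP, SPU, PUS} biases U − P by −2/3 L and S − P by 0, while six orders bias each by −1/3 L.

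All of this is correct, and it limits the point to an avoidable weakness. It does not restore the design. Baselines do not protect a comparison of post-phase values or cancel a decaying residual. The worst case for a single product's carryover is still twice as large with three cyclic orders, and adjustment costs far more.

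**Conclusion.** The point holds in a limited form. The article fixes three of six orders, and either reading has a weakness. A period-balanced set gives every product one fixed predecessor. Any other set leaves product partly confounded with period under a model that names no period term.

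In the cyclic case, with first-order carryover and post-phase comparison, the worst-case bias in a pairwise contrast is 2/3 of a product's carryover, against 1/3 with six equally used orders. Adjusting for carryover multiplies the standard error by √5.0 = 2.24 with three orders and by √1.25 = 1.12 with six. If there is no carryover, nothing is lost under either design. Nothing in the documents shows that carryover lasts beyond four weeks, so this is a gap in protection and not a demonstrated bias.

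**What to change.** Before the first enrolment:

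1. Generate the randomisation list over all six orders in blocks of six, and state the orders in the protocol.
2. Include period in the analysis model.
3. Compare the pre-phase samples at Visits 3 and 5 with Visit 1, according to the products already taken, as a carryover check. Report estimates with confidence intervals. With about 11 participants per first product, a nonsignificant result would not show that carryover is absent.

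The cost is a new computer-generated list, and the article reports no participants enrolled as of December 2025. The required 28 and the planned 33 can stay. Because 33 is not a multiple of six, orders may differ by one participant; 30 or 36 would balance exactly. Six orders reduce the worst-case bias but do not remove it, so the washout and the baselines still matter.
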